## Abstract

**Background:**

Studies show a high and growing prevalence of mental disorders in the population worldwide. 25% of the general population in Europe will during their lifetime experience symptoms related to a mental disorder. The Mental Health First Aid concept (MHFA) was founded in 2000 in Australia by Kitchener and Jorm, in order to provide the population with mental health first aid skills. The aim of the concept is, through an educational intervention (course), to increase confidence in how to help people suffering from mental health problems. Further, secondary aims are to increase the mental health literacy of the public by increasing knowledge, reduce stigma and initiate more supportive actions leading towards professional care. An investigation of the effect of MHFA offered a Danish population is needed.

**Methods:**

The design is a randomized waitlist-controlled superiority trial, in which 500 participants will be allocated to either the intervention group or the control group. The control group will attend the course six months later, hence waiting list design. From fall 2013 to spring 2014 participants will be educated to be “mental health first-aiders” following a manualized, two days MHFA course. All the participants will answer a questionnaire at base-line and at 6 months follow-up. The questionnaire is a back-translation of the questionnaire used in Australian trials. The trial will be complemented by a qualitative study, in which focus groups will be carried out.

**Discussion:**

Outcomes measured are sensitive to interpretation, hence a challenge to uniform. This trial will add to the use of a mixed-methods design and exemplify how it can strengthen the analysis and take up the challenge of a sensitive outcome.

**Trial registration:**

https://clinicaltrials.gov identifier NCT02334020.

## Background

The World Health Organization estimates a high and growing prevalence of mental disorders worldwide [1]. In Europe, a lifetime expectancy of mental health problems in the general population is estimated to be 25% [2]. Recent research from Denmark shows that the figures might even be higher – as many as 38% of the female population and 32% of the male population is expected to receive treatment in the secondary mental health sector [3].

The psycho-social and economic impact of mental disorders is considerable [4]. Early intervention can lower both the human and economic costs [4,5]. Even though the numbers might be high, we know that according to international epidemiological investigations, the rates of help-seeking behavior for mental health problems are generally low compared to how many people that actually suffers from mental health problems [6]. This is a problem because early help-seeking can enhance the opportunity for early intervention, and can therefore improve long-term outcomes.

There is evidence to suggest the effectiveness of community-based interventions in order to increase the help-seeking behavior of people with suicidal behavior [7]. The key element of such interventions is enhancing the knowledge of mental disorders through educational training of the general practitioners, municipal officials, and the general public [8]. Mental Health First Aid (MHFA) is based on such a concept.

MHFA was developed by Betty Kitchener and Anthony Jorm in Australia in 2000. The overarching aim of MHFA is to increase the mental health literacy of the general public. An increase in mental health literacy means an increased confidence in how to help people suffering from mental health problems by providing relevant knowledge, reducing stigma associated with mental illness, and providing guidance regarding supportive actions [9].

In Denmark, a report on stigma and mental illness concluded that the majority of the population in general has contact with people suffering from mental illness through e.g. their social network or workplace. At the same time, the report and others alike stated that most people suffering from mental illness have experienced discrimination [10-12]. Despite the reported contact, knowledge of mental illness is low in the general public, while there on the same time is a great interest in the public to gain more knowledge on the subject [10].

Although research to date has shown promising results of the MHFA, further replication is needed in order to ascertain the generalizability of the findings also to Danish social and cultural circumstances. Evaluations of MHFA from both Swedish and Australian trials show increased helping behavior, greater confidence in providing help to others, improved attitudes and decreased need for social distance to people with mental illnesses [13,14]. Furthermore, a qualitative study has reported that positive effects were experienced both intra-personally (through increased empathy, understanding, and confidence to act appropriately) as well as inter-personally (through increased capacity to handle crises, manage strained relationships, and offer help in an effective way) [15].

### Objective

The objective of the Danish evaluation is to investigate the effect of MHFA as an education-based intervention on increased confidence in help-giving behavior as primary outcome by comparing an intervention group and a waiting list group. Secondary outcome will be comparing increased knowledge of and improved positive attitudes towards people suffering from a mental health problem also between the intervention and the waiting list group.

Through qualitative data we wish to explore the process of becoming a mental health first-aider and the participants’ experience of the course.

### Hypothesis

We expect to find; a significant difference in confidence in helping a person suffering from mental illness between the intervention group and control group; a significant increase in knowledge of mental illness; and hopefully a significant improvement in attitudes and decrease in wish for social distance towards people suffering from mental illness [9,13,14].

## Methods/Design

The design of the study will combine concurrent and sequential elements within a mixed-methods convergent parallel design [16]. This choice of design is based on the nature of the objective of the research being both exploratory and confirmatory at the same time [17]. In the study, qualitative and quantitative data will be collected.

The design of the quantitative part is a randomized, waitlist-controlled superiority trial, in which 500 participants will be allocated to either the intervention group or the control group. The control group will attend the course 6 months later, hence waiting list design. From fall 2013 to spring 2014 participants will be educated “First Aid-helpers” following a manualized, two days MHFA course. All the participants will answer a questionnaire at baseline and at six months follow-up. Concurrently, the trial will be complemented by a qualitative study, in which five focus groups will be held with participants before and after they attend the course and participant observation will be carried out on the course.

### Recruitment to the quantitative survey – criteria for inclusion

The MHFA training program was initially developed for the general public [13]. However, international experiences show that participants most often have been people who in their line of work are in contact with many different individuals [14]. We will try to replicate that in this study.

Hence, the study will recruit employees of 10 different workplaces, including public, private and non-governmental organizations (NGOs) sectors. Possible workplaces could be social services and job centers in different catchment areas of Denmark and telephone helplines in NGOs. A characteristic of the sample would then be its geographical diversity but with some occupational homogeneity.

The recruitment will be managed by an independent assistant at The Danish Mental Health Foundation. Contact will be established to leading officials at the different workplaces and NGOs, with whom the organization of participation at the given workplace will be arranged according to firm logistics. Participation will be presented as an opportunity for an education-based training course, relevant to the participants’ work life as well as private life. Participation will be voluntary and the training course will be held during work hours. Informed consent will be required and held in qualitative parts of the study.

### Randomization and blinding

The randomization will be computer generated, provided by an independent research assistant. Allocated outcome will be informed to the leading contact at each workplace and then passed on to each participant. The randomization procedure will ensure adequate sequence generation and allocation concealment. Furthermore, the analysis of the quantitative data will be blinded. It will not be known to the researcher, which group was the intervention group or the control group before the analysis is done.

### The intervention – the MHFA training course

MHFA is a manualized, educational preventive strategy structured in a 12-hour course delivered over two days of training. The course will be carried out and managed by The Danish Mental Health Foundation.

MHFA is based on four training sessions of three hours each. The course gives an overview of the major categories of mental health disorders and crisis. The items presented include depression, anxiety, psychosis, and substance abuse. The crisis situations covered are; thoughts of suicide and suicidal behavior, self-harming behavior, panic attacks, reactions to trauma, acute psychosis, substance intoxication, and aggressive behavior. Participants are introduced to symptoms of the illness, possible risk factors, evidence-based treatment and where and how to get help [18]. The training will consist of a mix between knowledge-presentations and exercises, and a five-step action plan will be applied to each category of the mental health problems presented.

The action plan consists of a series of five steps, which include 1) Access risk of suicide or harm 2) Listen non-judgementally 3) Give reassurance and information 4) Encourage the person to get appropriate professional help, and 5) Encourage self-help strategies.

Further, the training involves cases and encourages the participants to bring in examples from their own experiences. All instructors are certified teachers and all experienced in working with people who have experienced mental health illness.

### Survey procedure

A link to the electronic questionnaires will be sent out at baseline and at six-month follow-up by email to the participants, primarily to their work email-address, in order to avoid loss to follow-up [14]. Reminders to complete questionnaires will be provided at both baseline and at follow-up.

The software program used for the distribution of the questionnaires will be Survey Xact [19].

### Instruments in the quantitative survey

The questionnaire is a back-translation of the questionnaire used in Australian trials [18]. It is translated into Danish and retranslated into English, thus validated in relation to language difference.

The questionnaire will start with a range of socio-demographic questions, motivation for participation, personal mental health history, and previous experience with persons suffering from mental illness, and what kind of help, if any, participants had offered in these situations.

Following, the primary outcome will be measured through three questions. The questions will address how confident the person feels 1) to contact a person with mental health problems 2) to talk to a person with mental health problems 3) to help a person with mental health problems. All three questions will be answered on a four step scale: “not confident at all”, “a little confident”, “quite confident”, and “very confident”. Furthermore, if the person answers “not confident at all”, he/she will have to answer another question on the primary cause for this within a five step scale: “lack of knowledge”, “afraid of saying something wrong”, “afraid of the person’s reaction”, “don’t know what to advice the person to do”, “it is too great a responsibility”.

The following questions will address the secondary outcome on increased knowledge, improved attitudes and decreased need for social distance. For this, the questionnaire contains vignettes on depression or schizophrenia as a descriptive part of suggested intervention and response options. According to possible intervening suggestions the answers will be given on a three categories scale: “helping”, “make it worse”, “no effect”.

The questionnaire will include two scales assessing social distance towards people suffering from a mental illness. The same vignettes as before mentioned will be used in the attitude assessment, which will have to be answered within a five categories scale: “fully agree”, “partly agree”, “neither agree, nor disagree”, “partly disagree”, “fully disagree”. Assessments will address the participant’s point of view for both him/her-self and for the public in general. In the first scale the respondent will be asked to state, “to which extent yourself…” and in the second scale “what you think other people think”.

The last part of the questionnaire will consist of knowledge-questions concerning how to act around people suffering from a mental illness and which treatment strategies that are most appropriate. The questions will have to be answered within the categories: “Agree”, “disagree”, “Don’t know”.

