### Analysis outline

Primary outcome in the quantitative study will be increased confidence in providing help in situations where people are in a mental health crisis or experiencing a mental health problem by comparing the intervention group after having attended the training course with the control group. Secondary outcome will be increase in knowledge about mental health problems and crisis and options for professional reference as well as an increase in positive attitudes towards people suffering from mental health problems also by comparison of the two groups. Power analysis was performed using PS – Power and Sample Size Calculation. We calculated that with alpha = 0.05, a power of 0.8 and a standard deviation 0.75, and a smallest clinically relevant difference in means between the groups of 0.19 we would require 250 persons per group.

Continuous outcome measures will be analyzed using generalized linear models including treatment allocation, test of interaction term between allocation and the vignette used, as well as variables associated with attrition or baseline imbalances between the groups, if any. Missing data is expected to be missing at random and handled using multiple imputations. Dichotomous outcome measures will be analyzed using binary logistic regression in the same manner. To describe the reliability of the data from the attitudes questions: “What you think” contra “what others think”, we will analyse by using Cronbach’s Alpha. The case and knowledge based items in the questionnaire will be ranked where high scores equal right answers. Data will be analysed using IBM SPSS version 22.

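### The article does not say how the three confidence items become the single primary variable that the stated alpha, SD and difference refer to

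*Protocol article*

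**What the plan says.** Under Instruments in the quantitative survey, the protocol article states that "the primary outcome will be measured through three questions": confidence to contact, to talk to, and to help a person with mental health problems. It adds that "All three questions will be answered on a four step scale".

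The Analysis outline describes the endpoint in general terms: "Primary outcome in the quantitative study will be increased confidence in providing help in situations where people are in a mental health crisis" (the sentence continues). It names no item, sum, mean or cut-off. The power calculation there uses "alpha = 0.05, a power of 0.8 and a standard deviation 0.75" and "a smallest clinically relevant difference in means between the groups of 0.19", giving 250 per group. The variable behind these figures is not named.

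The same section assigns continuous measures to generalized linear models, and says "Dichotomous outcome measures will be analyzed using binary logistic regression in the same manner". It does not say which of the two covers confidence. The only scoring rule is for the case and knowledge items, and Cronbach's alpha is planned only for the attitude questions. Covariates enter the model only if they are related to attrition or unbalanced at baseline.

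**The concern.** A sample size belongs to a particular test on a particular variable. Here the calculation assumes one numeric variable, while the instrument yields three ordered items. The article gives no step between them: no composite, no lead item, no division of alpha.

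Two things are at stake. First, the power at 250 per group depends on which variable is tested, so the stated 0.8 cannot be checked against the primary analysis. Second, the choice of variable stays open until the data are in, and some of the permitted choices would not hold the error rate at 5%. The analyst's blinding to group identity, described under Randomization and blinding, helps only in part. Someone comparing two unlabelled groups can still see which item or score separates them.

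**Working it through.** **Inputs.** From the Analysis outline: alpha 0.05, power 0.80, SD 0.75, difference 0.19, 250 per group. From Instruments in the quantitative survey: three items of four steps each. The article gives no inter-item correlation ρ, so ρ is assumed and shown over a range. It does not state whether the test is one- or two-sided.

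**1. The plan's own figure.** n per group = 2 × (1.960 + 0.842)² × (0.75/0.19)² ≈ 245. The t-test version gives 245.6, so 246. A one-sided test would need 193, so the stated 250 corresponds to a two-sided test.

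Power at 250: the standard error is 0.75 × √(2/250) = 0.0671, and 0.19/0.0671 = 2.83. Power = Φ(2.83 − 1.96) = 0.81. The figure reproduces for one two-sided comparison of means on one numeric variable.

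**2. The same 250 per group under different readings.** Except in the first row, each item is taken to have SD 0.75. A true difference of 0.19 applies to each item, except in the row for the sum.

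| Reading | Working | Result |
|---|---|---|
| One variable (a named item or a mean score) with SD 0.75 and difference 0.19 | as in step 1 | power 0.81; the sample size stands |
| Mean of three items | SD = 0.75 × √((1 + 2ρ)/3) = 0.61 at ρ 0.5, 0.70 at ρ 0.8 | power 0.93 and 0.86 |
| Sum of three items, with 0.19 on the sum | SD = 3 × SD of the mean = 1.84 at ρ 0.5, 2.10 at ρ 0.8 | power 0.21 and 0.17 (0.37 at ρ 0) |
| Each item at 0.05/3 (Bonferroni) | Φ(2.83 − 2.39) | power 0.67 per item; 327 per group for 0.80 |

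**3. Error rate if each item were tested at 0.05 and any success counted.** With independent items, 1 − 0.95³ = 0.143. Simulation of 1,000,000 trivariate normal draws gives 0.125 at ρ 0.5, 0.109 at ρ 0.7 and 0.098 at ρ 0.8.

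**4. Which variable does 0.75 fit?** A single item scored 1 to 4 and a mean of three such items lie on the same scale, and either could have an SD of 0.75. A 3-to-12 sum is less likely: at ρ 0.5 it would imply a per-item SD of 0.75/√6 = 0.31, narrow for a four-step answer. The figure therefore does not settle whether an item or a mean was meant.

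**The case against.** The strongest reply is that the article speaks throughout of one primary outcome, confidence, measured by three questions. The Objective and the Hypothesis do the same. With one SD and one difference in means, the natural reading is one numeric score. If that score is the mean, with SD 0.75, then alpha, SD, difference and sample size all belong to one test and nothing is inflated. The section is also only an outline, and item scoring and multiplicity rules are often left to an analysis plan.

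Much of this stands, and it rules out several stronger conclusions that a reader might draw:

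- **That the trial plans to claim success on any of three items.** No section says so. The 10% to 14% error rate describes something the wording leaves open, not a stated plan.
- **That confidence will be analysed in two codings, or that dichotomising will cost the stated power.** The logistic sentence is generic, no cut-point for confidence appears, and a difference in means points to numeric scoring.
- **That an ordinal model is required.** Numeric scoring of such items, or of their mean, is common and fits the planned continuous model.
- **That an SD of 0.75 shows a single item was meant.** It could equally be the SD of the three-item mean.

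What does not stand is that the gap is only a detail for the analysis plan. The variable that the sample size rests on belongs with the sample size. The article gives a scoring rule for the case and knowledge items and none for its primary outcome.

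**Conclusion.** The point holds as a gap in definition. The sample-size arithmetic is correct, but the variable it applies to is not identified, so the 5% and the 80% do not belong to a stated primary test.

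The size of the problem depends on what was intended. If 0.19 and 0.75 are on the scale of a three-item mean, or of one named item, the power is 0.81 and only a sentence is missing. Other readings that the text permits give power at 250 per group from about 0.2 (0.19 on the sum, ρ 0.5 to 0.8) to 0.93 (mean, ρ 0.5). Uncorrected testing of the three items, with any success counting, gives a familywise error of about 10% to 14%. These alternatives rest on assumed correlations, and the power figures also assume a per-item SD of 0.75. They show why the variable must be named, and they do not predict what the trial will do.

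**What to change.** Name one primary endpoint: the mean of the three confidence items, each scored 1 to 4, at six months. Analyse it with the continuous model already in the Analysis outline, in one two-sided test at 0.05. Always adjust for the baseline mean score. The trial already collects it, but the present text would include it only if it proved unbalanced or related to attrition. Report the three items separately as secondary outcomes.

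State whether 0.75 and 0.19 are on that mean-score scale. If they are, the 250 per group stands as calculated. If they are per-item figures, restate the power for the mean with an explicit assumed correlation. With 0.19 on every item, it would be 0.93 at ρ 0.5 and 0.86 at ρ 0.8, so on that reading the change does not require more participants.

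The cost is a few sentences and, if needed, a re-run of the power calculation. The downside is that no single item, such as confidence to help, could then be claimed as a primary result.

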### Focus groups

Focus groups will be conducted before and after participants attend the course. The selection of participants to the focus groups will be non-strategic and criteria for participation will be expressed interest in discussion themes related to mental illness and completion of baseline questionnaire. Randomization allocation outcome will still be unknown to investigating researcher.

We plan to conduct three-five focus groups before and after the course, with four-six persons in each group. Each focus group will last 1.5-2 hours. The focus group interview will be loosely structured around an interview guide. The interview guide consists of both questions and ice-breaking exercises and focusing exercises [20].

The interviews will be led by investigating facilitator, observed and recorded in writing by an observer, and audio recorded and transcribed by a research assistant.

### Participant observation

Participant observation will be conducted on two of the MHFA courses, structured by an observation guide. The investigator will participate in the course on equal terms as the participants; participate in exercises and in discussions. This is to gain an understanding of the empirical setting in which data should be understood [20]. Further, participant observation will provide data on specific social negotiations of behavior and attitudes in the group of participants.

The notes will be transcribed shortly after and gathered in an early-analytical document in which observational notes and initial interpretations, analytic comments and views will be kept separately to avoid contamination of subsequent analysis.

